## Background

Preterm birth remains poorly understood in modern society despite accounting for 75% of perinatal mortality [1,2]. Moreover, the rate of preterm birth, that is birth before 37 completed weeks of gestation, has been on the rise for the past 3 decades in many developed countries including Canada, the USA and European nations where current rates range between 5-12% [3]. Infants born preterm are at increased risks for neonatal complications and associated long-term morbidity [4] such as developmental delays, hearing and vision impairments, respiratory distress syndrome, cerebral palsy and retinopathy of prematurity, prolonging the financial, emotional and stress-related costs of prematurity well beyond the care received within neonatal intensive care units. The risk for adverse neonatal outcomes is inversely related to gestational age at birth with the highest morbidity among those infants delivered prior to 28 completed weeks of pregnancy (early preterm) [5] despite technological advances and improved medical treatments having greatly increased the survival of these infants [6,7]. The rate of late preterm births (34-36 weeks gestation) has also continued to climb and accounts for 75% of all preterm infants [8]. Recent studies have shown that these late preterm infants are at higher risk for adverse acute and long-term outcomes when compared to term infants [9].

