### Sample Size

Sample size calculations for the All Our Babies Cohort Study required complex considerations as maternal blood samples are destined for microarray analyses. Several power calculations for microarray methodologies exist, consequently sample size was determined and compared with two power calculation approaches. The first approach uses a two-class comparison model with a significance level of 0.001, a power of 0.95, one technical replicate per sample and estimated values of τ^2 ^+ 2 γ^2 ^= 0.25 and τ^2^/γ^2 ^= 4 (where τ^2 ^is the biological variance within class of log ratios and γ^2 ^is the technical variance of log ratios); the minimum sample size to identify a two-fold change in gene expression between classes is thus 25 patients in each study group [42,43]. An alternate approach is to consider the sample size required to detect a two-fold change in the expression levels of the 90% and 75% least-variable genes for a given set of false positive rates and power [42]; using previously published human tissue microarray data [43] and setting the false positive rates at 0.001 and a power of 0.9, this approach gave a minimum of 18 and 13 patients in each group to detect a two-fold change in expression levels for the 90% and 75% least-variable genes, respectively. Microarrays will be performed on RNA samples collected from 80 cases of spontaneous preterm birth and 80 matched controls (160 biological replicates) from samples collected at two time points (18-22 weeks and 28-32 weeks): a total of 320 microarrays. This sample size will allow prediction of:

1) idiopathic PTB (n~40), including

a) idiopathic PTB prior to 32 weeks gestation (n~13); and

b) idiopathic PTB between 32 and 37 weeks gestation (n~27);

2) PPROM and PTB (n~40), including

a) PPROM and PTB prior to 32 weeks gestation (n~13);

b) PPROM and PTB between 32 and 37 weeks gestation (n~27);

3) spontaneous PTB (n~80), including

a) spontaneous PTB prior to 32 weeks (n~25); and

b) spontaneous PTB between 32 and 37 weeks gestation (n~55).

Therefore, with a preterm birth rate of 9.1% in Alberta, an anticipated miscarriage rate of 5% and an anticipated loss to follow-up rate of 15% based on experience with other Alberta based cohorts [44], 2200 women will be enrolled in the All Our Babies Cohort Study. This should ensure 1800 women complete the study, of which approximately 180 will have preterm birth outcomes and approximately 120 of these will be spontaneous with or without PPROM.

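### The two n~13 strata before 32 weeks fall below two of the plan's three per-group minimums, and both the early counts and the figure of 25 per group need a stated basis

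*Protocol article*

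**What the plan says.** All of the following is in the protocol article.

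- **Sample Size, first approach.** The inputs are "a significance level of 0.001, a power of 0.95, one technical replicate per sample" and "estimated values of τ^2 ^+ 2 γ^2 ^= 0.25 and τ^2^/γ^2 ^= 4". The result is that "the minimum sample size to identify a two-fold change in gene expression between classes is thus 25 patients in each study group".
- **Sample Size, second approach.** With "setting the false positive rates at 0.001 and a power of 0.9", "this approach gave a minimum of 18 and 13 patients in each group". The 18 is for the 90% least-variable genes and the 13 for the 75% least-variable genes.
- **Sample Size, strata.** Arrays are planned for 80 spontaneous preterm cases and 80 matched controls. The section says this size permits prediction in each listed stratum. Before 32 weeks these are "idiopathic PTB prior to 32 weeks gestation (n~13"), PPROM (n~13) and all spontaneous preterm births (n~25). About 120 spontaneous preterm births are expected in the cohort.
- **Background.** "The rate of late preterm births (34-36 weeks gestation) has also continued to climb and accounts for 75% of all preterm infants".
- **Obstetrical and Birth Record Data** refers to selecting cases for the genetic analyses. **Transcriptomic Analysis** describes loose matching on the distributions of maternal age, body mass index and smoking. Neither mentions selection by gestational age.

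**The concern.** Three things do not fit together.

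1. The plan sets its own minimums and then claims a capability in two strata that miss two of them.
2. The counts before 32 weeks have no stated source and are large beside the only gestational-age distribution that the article gives.
3. The largest minimum, 25 per group, depends on a log base that is not stated.

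A reader of the trial report would take the two early phenotype strata as adequately sized. If they are not, a finding of no difference there could be over-read. The calculations also concern detection of a two-fold change in a single gene. None of them addresses predictive accuracy, so the word prediction goes beyond them in every stratum.

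**Working it through.** **Step 1: reproduce the 25.** Inputs (Sample Size): alpha 0.001, taken as two-sided; power 0.95; variance 0.25, so SD 0.5; two-fold change.

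n per group = 2 × 0.25 × (3.291 + 1.645)² / δ², with (3.291 + 1.645)² = 24.36.

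| Log base | δ | Per group (normal) | Per group (t) | Total (normal) |
|---|---|---|---|---|
| log2 | 1 | 12.2 | 15 | 24.4 |
| natural | 0.693 | 25.3 | 29 | 50.7 |

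On log2, 25 matches the total for both classes. On natural logs it is close to the per-group figure: exactly 25 per group gives 94.6% power by the normal formula. The 18 and 13 cannot be reproduced, because the gene-variance data are not in the article.

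**Step 2: compare n~13 with the stated minimums.** 13 < 25, 13 < 18, 13 = 13. Two are missed, and the weakest is met with no reserve. The pooled n~25 meets all three, the highest of them exactly.

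**Step 3: power of 13 v 13.**

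- *At the variance behind the 18.* Find the SD at which 18 per group gives 90% power at alpha 0.001. By the t test it is 0.603 of a two-fold change, and 13 v 13 then gives 68%. By the normal formula it is 0.656, and the power is 72%. Only the ratio of SD to effect matters, so the log base does not affect this result.
- *On the first approach's inputs.* On log2, 13 v 13 gives 96% (normal) or 89% (t). On natural logs it gives 60% (normal) or 44% (t). The stated power is 95%.

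**Step 4: 13 cases against all 80 controls.** The equivalent equal group size is 2 / (1/13 + 1/80) = 22.4. This is above 18 and below 25. At the variance behind the 18, power is 96% (normal) or 98% (t). On the first approach's inputs it exceeds 99% on log2. On natural logs it is 91% (normal) or 89% (t).

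**Step 5: the share before 32 weeks.**

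- Stated: 13/40 = 32.5%; 25/80 = 31.25%. That 13 + 13 differs from 25 is rounding.
- Background: 100% − 75% = 25% before 34 weeks, so no more than that before 32 weeks.
- Applied to 80 unselected cases: 0.25 × 80 = 20 before 34 weeks, or 10 per phenotype of 40. Ten is below all three minimums.
- Applied to the pool of 120: 0.25 × 120 = 30 before 34 weeks. Reaching 25 before 32 weeks would need 25/30 = 83% of those births to fall before 32 weeks, and nearly all of them to be chosen for arrays.

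**The case against.** **The early counts do not strictly contradict the Background.** A reader might infer a contradiction, but the documents do not support it. The 75% is a cited figure for all preterm infants, including iatrogenic births. The 80 cases are a selected subset of about 120 spontaneous ones, and up to 30 of those could be before 34 weeks. This objection stands. What remains is a share with no stated basis that looks high, and a selection rule that it would need but that is not given.

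**The 25 is not a proven error.** A reader might conclude that a two-class total was printed as a per-group number. The article does not state the log base, and natural logs give 25.3. This also stands, and it affects the count of missed minimums: if log2 was used, the normal formula gives 13 per group, and n~13 would then miss only the 18 (the t version gives 15). But neither reading leaves the section as it is. On log2 the printed minimum disagrees with its inputs. On natural logs, 13 v 13 is well short of 95%.

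**The plan does not commit to 13 v 13.** Matching is at group level and the analysis uses the full dataset, so all 80 controls are available. A reader might infer that null results in these strata are bound to be uninformative; Step 4 shows otherwise. The plan does not state the larger comparison, however, and its minimums are expressed per equal group.

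**The claim is not unsupported for every stratum before 32 weeks.** The pooled n~25 meets all three minimums, provided that the count is reached.

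**Conclusion.** The point holds in limited form. For the two phenotype strata before 32 weeks, the claimed capability is not supported by the plan's own thresholds. At face value n~13 misses 25 and 18, and 13 v 13 has about 68% power where 18 per group has 90%. The pooled stratum is adequate on the stated minimums only if about 25 cases materialise, and that count has no stated basis. The 25 per group is unconfirmed until the log base is known.

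The assumptions are a two-sided alpha of 0.001, equal groups unless stated otherwise, and, for Step 5 only, that the 75% share carries over to spontaneous births. The article gives no share before 32 weeks, so the true stratum sizes cannot be computed from it. This should be corrected, but it does not undermine the main comparison of 80 cases with 80 controls.

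**What to change.** 1. Restate the early stratum counts from a stated gestational-age distribution, or state that early cases are preferentially selected from the spontaneous cases and by what rule.
2. Specify that each stratum is compared with all 80 loosely matched controls, adjusting for maternal age, body mass index and smoking. With 13 cases this equals about 22 per group, which clears 18 but not 25.
3. Replace the prediction claim with detection of two-fold expression differences, and label the idiopathic and PPROM strata before 32 weeks exploratory.
4. State the log base of the first approach, check it against the method used, and confirm or correct the 25.

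The cost is a less favourable description of the small strata and a little analysis work. No further patients or arrays are needed.

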### Inclusion Criteria

Inclusion criteria for the All Our Babies Cohort Study are designed to ensure women most at risk of preterm birth are captured in the cohort.

1. Women <17 weeks 6 days gestation at time of recruitment

2. Women receiving prenatal care in Calgary

3. Women able to understand written and spoken English

4. Age 18 years or older at time of enrollment

5. One of the following pregnancy histories:

a. Nulliparous or primiparous OR

b. A personal or familial history of preterm birth

6. Singleton pregnancy

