### Exclusion Criteria

1. Planned to move outside of the greater Calgary area during their pregnancy

2. Known to be carrying multiples at the time of enrollment

3. Had any of the following pre-existing medical conditions

a. Type I or Type II diabetes

b. High blood pressure or hypertension

c. Autoimmune/immune disorders: lupus, rheumatoid arthritis, Sjogren's syndrome

d. Kidney disease, chronic renal disease, nephritis, nephropathy, dialysis

e. A heart problem that was repaired by surgery

f. Chronic infection: hepatitis, HIV

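### The expected case yield rests on Alberta's provincial preterm rate of 9.1%, which is not justified for this selected cohort, and the stated counts do not follow from it

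*Protocol article*

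**What the plan says.** The Sample Size section of the protocol article starts the yield calculation "with a preterm birth rate of 9.1% in Alberta, an anticipated miscarriage rate of 5" per cent, and adds "an anticipated loss to follow-up rate of 15% based on experience with other Alberta based cohorts". From these inputs it concludes that "2200 women will be enrolled in the All Our Babies Cohort Study". It continues: "This should ensure 1800 women complete the study, of which approximately 180 will have preterm birth outcomes". About 120 of those births are expected to be spontaneous, with or without PPROM. From them, 80 cases are to go to microarray at two time points, including about 40 with PPROM.

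The eligibility rules describe a selected population:

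- Inclusion criterion 6 is "Singleton pregnancy", and the Exclusion Criteria also bar women "Known to be carrying multiples at the time of enrollment".
- The Exclusion Criteria remove women who "Had any of the following pre-existing medical conditions": diabetes, hypertension, autoimmune disorders, kidney disease, a surgically repaired heart problem, or chronic infection.
- Inclusion criterion 5 admits women who are nulliparous or primiparous, or who have a personal or family history of preterm birth. The section says that the criteria are meant to bring the women at highest risk into the cohort.

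The article does not say whether the 9.1% includes multiple pregnancies. It gives no rate for the eligible population and no reason for carrying the provincial rate over.

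**The concern.** The number of spontaneous preterm births is what the enrolment target was set to deliver, and the preterm rate is the input that drives it. A provincial rate reflects the provincial mix of pregnancies. Removing multiples, and women with conditions that can lead to early delivery, would be expected to lower the rate. Admitting women because of a preterm history would be expected to raise it. The article neither adjusts for these selections nor argues that they cancel.

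A second problem sits in the same sentence: the counts of 180 and 120 do not correspond to 9.1%. The reader therefore cannot tell which rate the study was planned on.

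At stake is the margin between the spontaneous births available and the 80 to be arrayed, and the size of the PPROM stratum. Each case is meant to supply RNA at both draws (320 arrays from 160 women), so some margin is needed. A woman who delivers before 28 weeks cannot give the second sample.

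**Working it through.** **Inputs from the article.** Enrolment 2200, miscarriage 5%, loss 15%, preterm rate 9.1%, stated completers 1800, stated preterm births 180, stated spontaneous births 120, array cases 80 (all Sample Size). PPROM share of preterm births 25-30% and iatrogenic share 30-35% (Background).

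**Step 1: the plan's own figures.**

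- Completers: 2200 × 0.95 × 0.85 = 1776.5, or 2200 × 0.80 = 1760 if the losses are added. Both agree with 1800 to within 3%.
- Spontaneous share: 120 / 180 = 2/3. This fits the Background, where 30-35% iatrogenic leaves 65-70%.
- Preterm births: 1800 × 0.091 = 163.8, and 1776.5 × 0.091 = 161.7. The stated 180 is 180 / 1800 = 10.0%, so this step does not reproduce. The Abstract's cohort of 2000 would give 2000 × 0.091 = 182, but the Sample Size text takes the 180 out of 1800.
- Spontaneous births at 9.1%: 163.8 × 2/3 = 109.2, or 161.7 × 2/3 = 107.8, not 120.

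The right baseline for judging the choice of rate is therefore about 108 spontaneous births. From these, 80 cases need 80 / 107.8 = 74% capture. The stated counts imply 80 / 120 = 67%.

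**Step 2: illustration of the singleton restriction.** The article gives no singleton rate, so this step is an assumption. Suppose the 9.1% covers all births, multiples are a share *m* of births, and a proportion *r* of them are preterm. Then

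singleton rate = (0.091 − *m* × *r*) / (1 − *m*).

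Applied to 1776.5 completers with the 2/3 spontaneous share:

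| *m* | *r* | Singleton rate | Preterm | Spontaneous | Capture needed for 80 |
|---|---|---|---|---|---|
| 0.02 | 0.5 | 8.27% | 147 | 98 | 82% |
| 0.03 | 0.5 | 7.84% | 139 | 93 | 86% |
| 0.03 | 0.6 | 7.53% | 134 | 89 | 90% |
| 0.04 | 0.6 | 6.98% | 124 | 83 | 97% |

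For example, the first row is (0.091 − 0.010) / 0.98 = 0.0827; 0.0827 × 1776.5 = 147; 147 × 2/3 = 98; 80 / 98 = 82%.

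The table leaves out the medical exclusions and criterion 5.

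**Step 3: PPROM pool.** In this scenario, 0.25 × 124 = 31 to 0.30 × 147 = 44, for about 40 places. At an unadjusted 9.1%, 0.25 × 161.7 = 40 to 0.30 × 161.7 = 49.

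**Step 4: break-even.** Eighty spontaneous births require a rate of 80 / (1800 × 2/3) = 6.7% (6.8% with 1776.5 completers). This assumes that every case is captured.

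**Step 5: enrichment that would cancel the shift.** Returning from 8.27% or 6.98% to 9.1% takes a relative increase of 9.1 / 8.27 = 1.10 to 9.1 / 6.98 = 1.30, that is 10-30%.

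**The case against.** The strongest reply is that the net effect of eligibility is unknown. Criterion 5 is an enrichment rule, and the Background names preterm history as a strong risk factor. An increase of 10-30% would offset the whole singleton adjustment. This stands. A reader might infer from the exclusions that the cohort's rate must fall below 9.1%, but the documents do not support that. It is equally true that criterion 5 admits every nulliparous or primiparous woman whatever her risk, and that the article never quantifies the enrichment or uses it to defend 9.1%.

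A reader might also set 83-98 spontaneous births against the stated 120 and blame the provincial rate for the whole gap. That is not right either. Part of the gap is the mismatch between 9.1% and 10.0%. The choice of rate moves about 108 to 83-98.

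Nor do the figures show that the 80 cases are out of reach. Every scenario in the table leaves more than 80. Preterm deliveries are identified by chart extraction, so a woman lost to questionnaires need not be lost as a case. As an upper bound, 2200 × 0.95 = 2090 women at 6.98-8.27% with the 2/3 share give 97-115 spontaneous births, and 80 cases need about 69-82% of them. The PPROM target is approximate, and 31 still exceeds the 25 per group that the first power calculation requires.

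Finally, the illustration holds the spontaneous and PPROM shares fixed. If multiples and chronic disease contribute mainly iatrogenic births, which is an inference, the total of 180 would fall more than the spontaneous pool. That weakens the illustration, but not the point that the rate is unsupported.

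The article may condense a fuller derivation. However, it prints the rate and the counts as its basis for 2200, and these do not agree with each other.

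**Conclusion.** The point holds in a limited form. The 9.1% is a provincial rate, carried without justification to a cohort that is selected in both directions. The documents do not fix the direction or size of the error.

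The part that needs no outside assumption is the mismatch in the counts: 9.1% of 1777-1800 completers is about 162-164 preterm and 108-109 spontaneous births, not 180 and 120.

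The part that rests on assumptions is the singleton effect. If the 9.1% includes multiples at 2-4% of births with 50-60% of them preterm, and the 2/3 spontaneous share is kept, the yield is 124-147 preterm and about 83-98 spontaneous births before any enrichment. The 80 cases remain reachable, but the capture needed rises from 74% to 82-97%. The PPROM pool of 31-44 may or may not fill about 40 places. The consequence is a thinner and less certain margin than the article conveys, not a demonstrated shortfall.

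**What to change.** In the Sample Size section:

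1. Replace 9.1% with a preterm rate for the eligible population: singletons without the excluded conditions, with the criterion 5 mix where the data allow. Tabulate it from the provincial perinatal database that the study already links to, and state its source and whether multiples are included.
2. Restate the expected preterm, spontaneous and PPROM counts as a range that follows from that rate and from the completer number, so that rate, completers and counts agree.
3. Describe the array set and its strata as the numbers expected within that range, with up to 80 spontaneous cases.

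The cost is one database tabulation and a rewritten paragraph. The stated yields may become less favourable. Enrolment and study procedures do not change.

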**Methods/Design:**

Collaborations have been established between clinical lab services, the provincial health service provider and researchers to create an interdisciplinary study design for the All Our Babies Study. A birth cohort of 2000 women has been established to address this research question. Women provide informed consent for blood sample collection, linkage to medical records and complete questionnaires related to prenatal health, service utilization, social support, emotional and physical health, demographics, and breast and infant feeding. Maternal blood samples are collected in PAXgene™ RNA tubes between 18-22 and 28-32 weeks gestation for transcriptomic analyses.

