The pathophysiology of preterm birth is complex due to multi-factorial causes and its heterogeneous nature. Preterm birth is often categorized as (1) iatrogenic when delivery is a consequence of medical intervention (30-35%); (2) spontaneous when it occurs after spontaneous labour with intact membranes (40-45%); or (3) the result of preterm premature rupture of the membranes (PPROM) (25-30%) [3]. While gestational diabetes, preeclampsia and intrauterine growth restriction have all been associated with iatrogenic preterm birth, the underlying causes of spontaneous preterm birth are less clear. Reported risk factors are widespread and diverse, supporting the hypothesis of gene-gene and gene-environment interactions in the pathophysiology of spontaneous preterm birth. Highly associated risk factors include a previous preterm birth or a relative with preterm birth [10] or a black racial background [11], suggesting genetic causes. Other demographic factors such as low socioeconomic status [12] and maternal stress [13] have shown an association, indicating that the environment contributes to the etiology of spontaneous preterm birth.

Evidence for a causal role of infection and inflammation in preterm birth has been reviewed in detail [14]. Both interleukin (IL)-1β and tumor necrosis factor (TNF)α are cytokines produced by the intrauterine tissues in response to bacterial infections [15,16] which stimulate prostaglandin synthesis [17] and increase uterine contractility. Several groups have investigated the relationship between a single nucleotide polymorphism (SNP) located in the promoter of the TNFα gene (G-308>A) (referred to as the TNF-2 allele) and preterm birth, but inconsistent results have been reported [18-21]. A recent meta-analysis of seven studies [22] found no association between preterm parturition and the TNF-2 allele. Similarly, studies examining polymorphisms in IL-1β and IL-6 as well as other variants have also produced inconsistent results [19,23,24].

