### Anticipated Rate of Loss To Follow-Up

The All Our Babies Cohort Study anticipates retaining 85% of women after completion of the first questionnaire and excluding miscarriages. Based on women's consent to participate in follow-up studies of 97% and with dedicated retention strategies, it is anticipated that no more than 10% of study participants will be lost to follow-up into the preschool years.

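### The expected 180 preterm births among 1800 completers do not follow from the stated 9.1% rate, and the 120 spontaneous cases inherit the error

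*Protocol article*

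**What the plan says.** The last paragraph of the Sample Size section derives the enrolment target. Its inputs are "with a preterm birth rate of 9.1% in Alberta, an anticipated miscarriage rate of 5% and an anticipated loss to follow-up rate of 15" per cent, and its target is "2200 women will be enrolled in the All Our Babies Cohort Study". The result follows: "This should ensure 1800 women complete the study, of which approximately 180 will have preterm birth outcomes". About 120 of the preterm births are then expected to be spontaneous, with or without PPROM. Earlier in the section, 80 spontaneous cases and 80 controls are set aside for microarrays.

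Three other places bear on the calculation:

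- **Anticipated Rate of Loss To Follow-Up:** the study "anticipates retaining 85% of women after completion of the first questionnaire and excluding miscarriages". The 15% loss therefore applies to women who remain after miscarriages.
- **Background:** iatrogenic births are put at 30–35% of preterm births, which leaves 65–70% spontaneous or PPROM.
- **Abstract:** "A birth cohort of 2000 women has been established to address this research question", a different number from 2200.

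**The concern.** The paragraph presents 180 and 120 as the result of the rates it lists. The 180 is counted out of the 1800 completers, so the implied rate is 180/1800 = 10.0%, not 9.1%. The count of spontaneous cases rests on the same step.

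Two things are at stake. The 120 shows the reader how many spare cases stand behind the 80 to be arrayed, and 180 is the size of the preterm group in the whole-cohort comparisons of term and preterm deliveries. If both are too high, the reserve and the preterm group are smaller than the reader is told.

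**Working it through.** **Inputs.** Enrolment 2200, preterm rate 9.1%, miscarriage 5% and loss to follow-up 15% (Sample Size); 85% retention after miscarriages (Anticipated Rate of Loss To Follow-Up); iatrogenic share 30–35% (Background); 80 cases to be arrayed (Sample Size).

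**Step 1: completers (stated 1800).**
- Losses in sequence: 2200 × 0.95 × 0.85 = 1776.5, which is 1.3% below 1800.
- Losses added: 2200 × 0.80 = 1760, which is 2.2% below 1800.

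The stated figure reproduces within rounding.

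**Step 2: preterm births (stated about 180).**
- From the stated completers: 1800 × 0.091 = 163.8; 180/163.8 = 1.099.
- From the full chain: 1776.5 × 0.091 = 161.7; 180/161.7 = 1.113.

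The stated figure does not reproduce. It is 10–11% too high. With added losses the count is 1760 × 0.091 = 160.2, and the excess is 12%.

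**Step 3: spontaneous share (stated 120 of 180).**
- 120/180 = 66.7%, inside the 65–70% from the Background.

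This step is consistent.

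**Step 4: spontaneous cases with step 2 corrected (stated about 120).**

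| Preterm births | 65% | two thirds | 70% |
|---|---|---|---|
| 161.7 (full chain) | 105.1 | 107.8 | 113.2 |
| 163.8 (from 1800) | 106.5 | 109.2 | 114.7 |

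The range is about 105–115. Against it, 120 is too high by 120/114.7 − 1 = 4.7% at the least and 120/105.1 − 1 = 14.2% at the most.

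**Step 5: what this does to the array set.**
- Stated reserve: 120 − 80 = 40. Corrected: 105 − 80 = 25 to 115 − 80 = 35.
- Enrolment at which 80 spontaneous cases are expected: 80/(0.70 × 0.091 × 0.95 × 0.85) = 1555 to 80/(0.65 × 0.091 × 0.95 × 0.85) = 1675. Both are below 2200.

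**The case against.** **Can the 180 be rescued?** Three routes come close.

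- 2000 × 0.091 = 182, using the abstract's cohort. But the Sample Size text counts the 180 among the 1800 who complete.
- The inclusion criteria aim at women at higher risk, so a cohort rate near 10% is conceivable. But the paragraph relies on "with a preterm birth rate of 9.1% in Alberta", no higher rate is given, and the eligibility criteria also exclude multiples, diabetes and hypertension. This softens the error without curing it.
- For the 120 alone, the upper ends of the Background's spontaneous and PPROM shares (45% + 30% = 75%) give 161.7 × 0.75 = 121. That leaves 25% iatrogenic, outside the stated 30–35%.

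**Does it matter?** The strongest reply is that nothing in the design depends on the slip. The power calculations (25, 18 and 13 per group) use neither 180 nor 120, corrected cases still exceed 80, and the adequacy claim for the whole cohort is made for 1800 women, which holds. This stands, and it limits the severity.

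**Stronger readings that the protocol article does not support.**

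- *That 1800 is also wrong.* The difference from 1777 is rounding in a planning figure.
- *That the array strata must be re-derived.* They subdivide the fixed 80 cases and were not computed from 180 or 120. The supply of PPROM cases is thinner: at the Background's 25–30% share, 161.7 × 0.25 = 40 to 163.8 × 0.30 = 49, against about 40 wanted. That bears on feasibility and does not make the strata wrong.
- *That unreturned first questionnaires shrink the case pool further.* Preterm births are phenotyped by chart extraction (Obstetrical and Birth Record Data), and consent to blood collection and record access is signed at the first draw (Ethics). A woman who gave blood can be a case without having returned a questionnaire.
- *That no allowance exists for missed draws.* The surplus over 80 acts as one, though it is not labelled so. No draw-completion rate is given, so a shortfall cannot be asserted.
- *That the abstract's 2000 lowers every figure.* It may be an achieved or rounded count. Applying the attrition rates to it assumes that it is an enrolment target, which the abstract does not say.

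**Conclusion.** The point holds for one step. Going from 1800 completers to 180 preterm births uses an unstated 10% rate in place of the stated 9.1%. Preterm births are overstated by about 10–11% (162–164 expected), and spontaneous cases by about 5–14% (105–115 expected; 108–109 at the plan's own two thirds). The reserve above the 80 arrayed cases is about 25–35 instead of 40.

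This assumes that the 9.1% applies to the women who complete, as the text has it, and that the Background's 30–35% iatrogenic share applies to this cohort. A reader might infer that the microarray sample size or the enrolment target fails; the corrected counts do not support that. Severity is minor to moderate: the figures are part of the stated justification for enrolling 2200 and are wrong as written, but no design decision changes.

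**What to change.** In the Sample Size section, do one of the following:

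1. Keep 9.1% and restate the yield: 2200 enrolled, about 1800 completing, about 162–164 preterm, about 105–115 of these spontaneous with or without PPROM.
2. Keep 180 and 120, but state a 10% cohort rate and give the evidence that this cohort exceeds the provincial rate.

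In the first case, add that the reserve above the 80 arrayed cases is about 25–35. Separately, say whether the abstract's 2000 is an achieved or a planned number, and how it relates to 2200.

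The first option costs only wording, and the stated yield becomes slightly less favourable. The second also needs a source for the higher rate. Enrolment, the 80-case array set and its strata need not change.
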